### Statistical and machine learning analyses

Our dataset comprises both diagnosed and undiagnosed patients, enabling us to evaluate the quality of the data. The goal is to have a case-control ratio of 1:1 in the dataset. Specifically, records from patients diagnosed with endometriosis but not yet received treatment should highly correlate with well-known endometriosis-associated symptoms, such as pelvic pain.

The normal distribution of the data will be tested with histograms and QQ-plots. Continuous variables will be presented as averages (mean ± SD), nominal variables as numbers (n) and percentages (%). A level of statistical significance of P < 0.05 will be used. The VAS scores of the endometriosis group and the reference group will be compared with independent sample t-tests. Also, independent samples t-tests will be conducted to see whether EQ-5D-5L, CSI-9 and EHP-5 scores were different between diet-users and non-diet users. Subsequently, a one-way analysis of variance of no diet use and the various diets will be carried out for the EQ-5D-5L, CSI-9, and EHP-5 scores. A post-hoc multiple comparisons analysis (Tukey honestly significant difference) will be used to identify where the differences between these diet groups were located. Preliminary analyses will involve various correlation techniques and visual representations, including heat maps contrasting diseases against symptoms.

To explore associations between diseases, symptoms, severity, dietary habits, and lifestyle activities, we will employ Cramér’s V statistical method. Additional validation of patient segmentation will be conducted to confirm that emerging patient cohorts exhibit anticipated symptoms. Machine learning algorithms will be deployed to uncover hidden relationships or patterns. Density-Based Spatial Clustering of Applications with Noise (DBSCAN) and Uniform Manifold Approximation and Projection (UMAP) will be employed to visualize high-dimensional symptom and activity spaces in 2D or 3D representations for dimensionality reduction and clustering. Risk assessments for undiagnosed patients will be computed using Random Forest and Long Short-Term Memory (LSTM) models. The LSTM models will fully leverage the time-series data, offering predictive insights into disease outcomes based on the temporal progression of symptoms.

All the methodologies above will be tested under various scenarios, such as:

Including all available symptoms and lifestyle/dietary activities.Excluding variables considered irrelevant based on existing medical literature.Segmenting the analysis for diagnosed versus undiagnosed patients.

These tests will help validate whether the methodologies yield consistent and reliable results. Given the substantial volume of our dataset—exceeding a million patient records—the data should be sufficient to use novel Transformer network models for pattern recognition and predictive analytics for at least low-complexity cases.

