## Introduction

Endometriosis is a chronic inflammatory disease with endometrium-like tissue outside the uterine cavity [1, 2]. It is commonly associated with chronic pelvic pain, infertility, and decreased quality of life, although asymptomatic cases exist [3–5]. The exact prevalence of endometriosis is unknown, but it may affect 5–10% of women and those assigned female at birth during their reproductive years, which equals nearly 190 million people worldwide [1]. Despite this high prevalence, recognition of the disease is inadequate, underprioritized, and research is underfunded, contributing to diagnostic delays ranging from 4 to 11 years [6–9]. Accordingly, endometriosis should be considered a public health issue, and reducing the current diagnostic delay is paramount.

Lucy is a mobile health application (Lucy app) designed to alert users with an increased risk of endometriosis to seek medical attention. Users can input their menstrual cycle information, health status, medical records or diagnoses, dietary details, lifestyle, and pain symptoms. Specialists in reproductive gynecology and health psychologists developed the app’s algorithm to continuously analyze the recorded data and alert the user when the entered symptoms are strongly associated with endometriosis.

A baseline questionnaire and a longitudinal questionnaire were developed and implemented as an additional module in the Lucy app. It collects self-reported data on symptoms of endometriosis, socio-demographics, mental and physical health, economic factors, nutrition, and other lifestyle factors [10]. By linking the collected information with existing registry-based information on diagnoses of endometriosis, healthcare use, and the big data approach, we can develop a phenotype description of individuals with endometriosis and structured clinical data [11].

So far, only one study has investigated this question with big data analysis using machine learning (ML). According to Bendifallah *et al*., endometriosis can generally be diagnosed with high diagnostic accuracy based on endometriosis-related symptoms and demographic data using ML technology [12]. The work presented by these authors was based on medical records of 800 participants of a French cohort and not on patient self-reported data.

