### Eligibility criteria

5,000 women with confirmed endometriosis and 5,000 women without diagnosed endometriosis in a control group aged 18–45 years will be enrolled and followed up for one year.

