### Questionnaire

Participants will be asked to complete a baseline questionnaire once and a longitudinal questionnaire monthly for one year. The questionnaire includes questions about endometriosis symptoms, socio-demographic information, mental and physical health, known medical conditions, medication use, dietary habits, economic burden, and lifestyle factors. These include free-text responses, single or multiple-choice questions, and numerical rating scales. See Supplementary Data for the questionnaires and https://hellolucy.app/en/ for the Lucy app.

Self-reported data of the participants will be measured as follows:

Evaluating the quality of life using the 5-level EQ-5D (EQ-5D-5L) and Endometriosis Health Profile 5 (EHP-5) [18].Assessing pain scores using the Visual Analogue Scale (VAS) [19].Examining somatic and emotional symptoms associated with central pain sensitization using the short version of the Central Sensitization Inventory (CSI-9) [20].

If using the same user account, Lucy app users can pause and resume completing the questionnaire, even on different devices. Once all questions have been answered, users can review and modify their answers on a summary screen. When they submit the questionnaire, their responses are stored on a server. At this point, the questionnaire’s content is fixed and cannot be changed.

In longitudinal studies, minimizing the drop-out rate and encouraging maximum user participation in completing the desired quantity of questionnaires is crucial. *Lucy app* users are anonymous; therefore, personal email contact is impossible. To address this challenge and reduce dropouts, the application uses several methods to notify users when the questionnaire becomes available for completion again. The questionnaire menu is prominently displayed on the application’s main page, and a pop-up window alerts users that the questionnaire is complete. Users can track the number of times and when they completed the questionnaire, but detailed completion data is not visible. The app displays a pop-up window with motivational quotes and positive messages to encourage and support users. In addition, users who complete the questionnaire are entered into a drawing as an additional incentive to participate. These measures are designed to minimize dropout and maximize user engagement in completing the questionnaires for the study.

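### The only test named for VAS pain is an unadjusted t-test between self-selected groups; at 5,000 per group a small imbalance is enough to make P < 0.05 uninformative

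*Protocol article*

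**What the plan says.** All references are to the Protocol article.

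- **Test.** Statistical and machine learning analyses: "The VAS scores of the endometriosis group and the reference group will be compared with independent sample t-tests". The section names no covariate, time point or per-person summary for this test. On the threshold it says: "A level of statistical significance of P < 0.05 will be used".
- **Schedule.** Questionnaire: "Participants will be asked to complete a baseline questionnaire once and a longitudinal questionnaire monthly for one year". VAS is listed among the self-reported measures there.
- **Groups.** Eligibility criteria: "5,000 women with confirmed endometriosis and 5,000 women without diagnosed endometriosis in a control group aged 18–45 years". Recruitment is through the app in eight countries (Study design). On balance, the analysis section says only: "The goal is to have a case-control ratio of 1:1 in the dataset". That is a goal for group sizes, not matching on any characteristic.
- **Treatment.** The same analysis section singles out "records from patients diagnosed with endometriosis but not yet received treatment" as those whose data should correlate highly with known symptoms, and gives pelvic pain as the example.
- **Data at hand.** The questionnaire collects socio-demographic data and medication use (Questionnaire). On cycle data, the Introduction says: "Users can input their menstrual cycle information".

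Correlations, heat maps and Cramér's V may also touch pain as a symptom, but no adjustment is described for them. Random Forest and LSTM models are meant for risk prediction, not for a group comparison of VAS.

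**The concern.** Women in the two groups chose to use the app and differ by diagnosis, not by allocation. They may also differ in age, country and treatment. An unadjusted t-test attributes any resulting VAS difference to group membership. The usual comfort of a large sample works in reverse here: random error becomes so small that a modest systematic difference decides the result.

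Treatment deserves separate mention because the protocol itself links it to pain. It uses untreated cases as the reference for expected symptoms, yet the VAS test merges treated and untreated cases.

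The second issue is the unit of analysis. An independent-samples t-test needs one value per woman. The schedule can produce about 13 questionnaires each (1 baseline + 12 monthly), and the protocol does not say which value, or which summary of them, enters the test.

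**Working it through.** The protocol gives no SD, effect size, power or within-person correlation for VAS, so there is no figure of its own to reproduce. The calculations below work in SD units and show scale only.

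**Inputs from the protocol:** n = 5,000 per group (target enrolment); alpha 0.05, taken as two-sided because sidedness is not stated; 12 monthly records per woman.
**Assumed inputs:** confounding bias b of 0.01 to 0.10 SD; within-person correlation ρ of 0.3, 0.5 or 0.7.

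**Step 1. Precision with one value per woman.**
SE = √(2/n) = √(2/5,000) = 0.020 SD.
Detectable difference at 80% power = (1.96 + 0.842) × 0.020 = 0.056 SD.

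**Step 2. Effect of confounding bias when the disease itself makes no difference to VAS.**
P(reject) = Φ(b/SE − 1.96) + Φ(−b/SE − 1.96).
Coverage of the 95% CI = Φ(1.96 − b/SE) − Φ(−1.96 − b/SE).

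| Bias b (SD) | b/SE | P(reject) | CI coverage |
|---|---|---|---|
| 0.01 | 0.5 | 0.079 | 0.921 |
| 0.02 | 1.0 | 0.170 | 0.830 |
| 0.05 | 2.5 | 0.705 | 0.295 |
| 0.10 | 5.0 | 0.999 | 0.001 |

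The rejection column assumes no true difference. The coverage column applies whatever the true difference is, so it matters even if cases clearly have more pain.

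**Step 3. Pooling monthly records as if independent (conditional).**
Design effect DE = 1 + (12 − 1)ρ. Type I error = 2 × [1 − Φ(1.96/√DE)].

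| ρ | DE | SE too small by factor √DE | Type I error | Simulated, pooled | Simulated, person mean |
|---|---|---|---|---|---|
| 0.3 | 4.3 | 2.07 | 0.345 | 0.359 | 0.048 |
| 0.5 | 6.5 | 2.55 | 0.442 | 0.455 | 0.050 |
| 0.7 | 8.7 | 2.95 | 0.506 | 0.508 | 0.047 |

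The simulation used 300 women per group, 12 records each and 2,000 runs. With 13 records the type I error is 0.361, 0.459 and 0.523. One mean per woman restores the nominal level.

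**Step 4. Repeated data alone do not help with bias.**
The correct SE of a 12-record person-mean comparison is √(2·DE/(5,000 × 12)) = 0.0120, 0.0147 and 0.0170 SD for the three values of ρ. A bias of 0.05 SD is then 0.05/0.0120 = 4.2, 0.05/0.0147 = 3.4 and 0.05/0.0170 = 2.9 standard errors, against 2.5 with a single value. Using all the data without adjustment therefore makes the confounding problem sharper.

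**The case against.** The strongest reply is that no objective asks for a confounder-free pain difference between cases and controls. The primary objective is a data repository, profiling and earlier detection; the secondary ones concern diet, exercise and relaxation, and cost. The t-test can be read as crude description, and covariates or the choice of record can be left to a fuller plan. Part of this stands: the protocol nowhere calls the result an effect of endometriosis on pain. But it names this test with a significance threshold and does not label it descriptive, so the point concerns a stated choice and not only missing detail.

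Several stronger readings are tempting but not supported:

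- **A reader might infer that the standard error is wrong.** It is wrong only if several records per woman enter the test as independent. The protocol never says so, and one value or a mean per woman gives a valid standard error. That VAS is collected monthly is itself a fair reading of the Questionnaire section, not an explicit statement.
- **A reader might infer that the protocol shows VAS to depend on cycle phase, age and country.** Only treatment has support in the text; the rest is plausible assumption. Cycle entry may be optional, and nothing says it is linked to the date of the questionnaire.
- **A reader might try to size the dilution by treatment.** For example, 60% treated and a 1.5-point effect give 0.6 × 1.5 = 0.9 points. Neither input is in the protocol. A mean over all cases describes all cases correctly; it is biased only if untreated pain is the target. If women in more pain are treated more often, the observed contrast could even reverse.
- **A reader might infer that the monthly data go unused.** The LSTM models are planned to use the time series, although that does not supply a VAS group estimate.

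**Conclusion.** The point holds for confounding, whichever VAS value is used. The one test named for VAS makes no adjustment between self-selected groups for which no matching is described, while relevant covariates are collected and the protocol itself regards treatment as bearing on pain. At the planned size a bias of 0.05 SD, which is an assumption, gives about 70% false rejection and about 30% coverage. Even 0.02 SD gives 17% and 83%. If fewer than 5,000 per group contribute, the standard error grows and these figures soften, but the bias stays.

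On repeated measures, what holds is that the protocol does not fix the value compared. The 35–51% type I error is conditional on pooling and on ρ of 0.3–0.7, and should not be quoted as a property of the plan. This should be changed, but it does not undermine the primary objective.

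**What to change.** Make the VAS comparison a linear mixed model on the baseline and monthly scores, with a participant random intercept and fixed effects for group, month, age and country. Report the group difference with its 95% CI. Use cycle phase only in a sensitivity analysis, where it is recorded.

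Show the difference overall and, descriptively, for treated and untreated cases, using the medication data already collected. The split should stay descriptive because treatment may follow from the severity of pain.

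Keep the t-test on one baseline value per woman, labelled as an unadjusted description. If a mixed model is not wanted, a fixed time point or person mean solves the standard-error question, but an adjusted estimate is still needed.

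The cost is a few sentences, one standard model and some missing covariate data. Before the wording is final, confirm that VAS is in both questionnaires and that country is recorded, since neither is stated outright. Adjustment reduces confounding by the recorded factors; self-selection into the app remains and should be stated as a limitation.

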No evidence-based advice concerning effective dietary interventions can be given to women with endometriosis [13]. Specifically, the effect of red meat, sugar, soy, dairy products, gluten, and caffeine on symptoms in women with endometriosis has not yet been systematically recorded. Therefore, we aim to investigate the effects of dietary restriction of these components on changes in quality of life, pain, and central pain sensitization. With this information, we may be able to identify nutritional components that affect the quality of life and pain in women with endometriosis. Consequently, real-world data-based dietary recommendations could be generated.

The present study aims to investigate the association between self-reported data and the clinical presentation of endometriosis. This could contribute to the classification of novel etiologic endometriosis. Such etiological findings could help to identify patterns that may categorize novel clinical subgroups of the disease. In addition, developing patient profiles may provide a novel diagnostic tool for the non-invasive, early detection of endometriosis.

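### The stated diet tests on EQ-5D-5L, CSI-9 and EHP-5 are defined by diet use alone in a planned 1:1 case-control dataset, although the dietary conclusions are meant for women with endometriosis

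*Protocol article*

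**What the plan says.** **Population.** Under Eligibility criteria, "5,000 women with confirmed endometriosis and 5,000 women without diagnosed endometriosis in a control group aged 18–45 years will be enrolled". Under Statistical and machine learning analyses, "The goal is to have a case-control ratio of 1:1 in the dataset".

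**Diet tests.** The same section says that "independent samples t-tests will be conducted to see whether EQ-5D-5L, CSI-9 and EHP-5 scores were different between diet-users and non-diet users", and then that "a one-way analysis of variance of no diet use and the various diets will be carried out for the EQ-5D-5L, CSI-9, and EHP-5 scores", with Tukey's procedure to locate differences. The comparison groups are defined by diet use. Diagnosis appears neither as a restriction nor as an adjustment.

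**Purpose.** The Introduction hopes to "identify nutritional components that affect the quality of life and pain in women with endometriosis" and to derive dietary recommendations. The Abstract's conclusions and the closing Conclusions direct the diet question at the same women. The secondary objective on diet names no population.

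**Instruments.** The Questionnaire section lists EHP-5 beside EQ-5D-5L among the self-reported measures for participants, without limiting it to cases.

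**Scenarios.** The statistical section ends by saying that all the methods described will be tried under several scenarios, given as examples. One of them separates diagnosed from undiagnosed patients. The stated purpose is to see whether the methods give consistent and reliable results.

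**The concern.** The question is about women with endometriosis, but the tests as stated put no condition on diagnosis. Two separate problems follow.

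1. **Confounding and dilution (all three scores).** If women with endometriosis follow diets more often than controls and also score worse, a comparison by diet use carries part of the case-control difference. Dieting could then look harmful when it does nothing, or a real benefit could be masked. Even with equal diet use, an effect present only in cases is averaged with a null effect in controls.
2. **Meaning of the score (EHP-5 only).** EHP-5 is a health profile for endometriosis. If controls answer it, their scores are hard to interpret. If they do not, the EHP-5 test covers cases only, while the EQ-5D-5L and CSI-9 tests beside it may cover everyone. The article does not say which applies. EQ-5D-5L and CSI-9 are not endometriosis-specific by name, so for them the issue is confounding, not validity of the instrument.

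What is at stake is the basis for the dietary recommendations that the study hopes to make.

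**Working it through.** **Inputs from the article.** 5,000 cases and 5,000 controls, so controls are 5,000/10,000 = 50% of planned enrolment, in agreement with the 1:1 goal. For significance, "A level of statistical significance of P < 0.05 will be used"; two-sided is assumed. The article gives no diet-use shares, case-control score gap or SD for these scores, so there is no figure of its own to reproduce.

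**Assumed inputs.** No true diet effect; diet use pk = 30% in controls and pc = 30–60% in cases; case-control gap D = 0.5 or 0.8 within-group SD.

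**Formulas.**
- Share of cases among diet-users: a = pc/(pc + pk)
- Share of cases among non-users: b = (1 − pc)/[(1 − pc) + (1 − pk)]
- Spurious difference = D × (a − b)
- Standard error = √{[1 + D²a(1 − a)]/n_diet + [1 + D²b(1 − b)]/n_none}, with n_diet = 5,000(pc + pk) and n_none = 10,000 − n_diet
- Expected z = spurious difference / standard error; the rejection rate uses the normal approximation at two-sided 0.05

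**Worked case.** For pc = 0.40 and D = 0.5:
- a = 0.40/0.70 = 0.571 and b = 0.60/1.30 = 0.462, so a − b = 0.110
- Spurious difference = 0.5 × 0.110 = 0.055 SD
- n_diet = 3,500 and n_none = 6,500, so the standard error is 0.0216 and z = 2.54

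| Diet use, cases / controls | a | b | D | Spurious difference (SD) | Expected z | Rejection rate |
|---|---|---|---|---|---|---|
| 30% / 30% | 0.500 | 0.500 | 0.5 or 0.8 | 0 | 0 | 5% |
| 35% / 30% | 0.538 | 0.481 | 0.5 | 0.028 | 1.3 | 25% |
| 35% / 30% | 0.538 | 0.481 | 0.8 | 0.046 | 2.0 | 51% |
| 40% / 30% | 0.571 | 0.462 | 0.5 | 0.055 | 2.5 | 72% |
| 40% / 30% | 0.571 | 0.462 | 0.8 | 0.088 | 3.9 | 97% |
| 60% / 30% | 0.667 | 0.364 | 0.5 | 0.152 | 7.3 | about 100% |
| 60% / 30% | 0.667 | 0.364 | 0.8 | 0.242 | 11.3 | about 100% |

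**Dilution.** With equal diet use, cases are half of each diet group. An effect δ in cases and 0 in controls gives a pooled difference of 0.5δ + 0.5 × 0 = δ/2.

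**Precision after restricting to cases.** The detectable difference at 80% power is (1.960 + 0.842) × √(1/n_diet + 1/n_none). With 30% on a diet (assumed):
- 10,000 women: 2.802 × √(1/3,000 + 1/7,000) = 0.061 SD
- 5,000 women: 2.802 × √(1/1,500 + 1/3,500) = 0.086 SD

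**The case against.** **The split by diagnosis is already foreseen.** Read literally, the scenario clause covers the diet t-tests, ANOVA and Tukey comparisons, so a diagnosed-only run is planned. This stands, and it rules out the stronger reading that the plan cannot answer the diet question in women with endometriosis. It does not settle the matter. The scenarios are examples meant to check consistency, and nothing makes the diagnosed-only run the main diet analysis. If diet use differs by diagnosis, segmented and unsegmented results can disagree, and no rule says which one supports the recommendations. The clause also implies a diet test of EHP-5 in undiagnosed women.

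**Pooling is never stated.** This is true. A reader might infer that the tests are run across everyone because the preceding VAS sentence names the endometriosis and reference groups. That sentence only names the two sides of another contrast and shows no intention to pool. The point is that the test is fixed by diet use alone, and that definition does not match the question. An article may leave detail to a fuller document, but this one fixes the outcomes, tests and comparison groups.

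**Controls are not known to be disease-free.** They are "5,000 women without diagnosed endometriosis in a control group", and the study plans risk assessment for undiagnosed patients. It would be too strong to say that no control has endometriosis impact to report. Whether controls are shown EHP-5 depends on questionnaires in the supplement, which is not at hand.

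**The size rests on assumptions.** This stands. With equal diet use the bias is zero, and at the mild end rejection is 25%, so a false positive is not inevitable. The 50% share of controls is an enrolment target, and the share within each diet group is unknown.

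**These are not the only diet analyses.** Cramér's V is also applied to dietary habits. The point here concerns the tests of the three scores.

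**Conclusion.** The concern holds in this form: the main diet tests are defined without regard to diagnosis, the planned dataset is half controls, and the conclusions are meant for cases. The scenario list mitigates this but does not name the analysis that answers the question.

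Under the assumptions tabulated above, with diet use higher in cases than in controls, the spurious difference is about 0.03–0.24 SD, with rejection between 25% and nearly 100% against a nominal 5%. Confounding disappears if either diet use or scores do not differ by diagnosis. The article gives no figures that would show which situation applies. The halving of a cases-only effect assumes equal diet use in both groups.

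The instrument objection is confined to EHP-5.

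**What to change.** In Statistical and machine learning analyses, state that:

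- the main diet analyses (t-tests, one-way ANOVA and Tukey comparisons) are run in the confirmed-endometriosis group;
- EHP-5 is analysed in cases only, including under the scenario that separates patients by diagnosis;
- any EQ-5D-5L or CSI-9 diet result that includes controls is reported separately by group, or comes from a model adjusted for diagnosis with a diet-by-group term.

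The cost is a sentence or two of text and some precision, because the main diet tests use about 5,000 rather than 10,000 women. At the assumed 30% diet use, the study can still detect a small standardised difference. No change to recruitment follows from this, and controls remain available for the case-control and prediction work.

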**Conclusions:**

We aim to develop a phenotypic description of women with endometriosis by linking the collected data with existing registry-based information on endometriosis diagnosis, healthcare utilization, and big data approach. This may help to achieve earlier detection of endometriosis with pelvic pain and significantly reduce the current diagnostic delay. Additionally, we may identify dietary components that worsen the quality of life and pain in women with endometriosis, upon which we can create real-world data-based nutritional recommendations.

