### Secondary objectives

To explore whether there is an association between removing or restricting dietary components and quality of life, pain, and central sensitization.To investigate the connections between different types of exercise, relaxation techniques, and the symptoms or diagnosis of individuals.To measure the financial implications of specific diets and different dietary supplements.

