## Conclusions

Endometriosis affects up to 190 million women worldwide and remains unresolved mainly in terms of etiology and optimal treatment strategy. It is often associated with chronic pelvic pain, infertility, and reduced quality of life. Despite this high prevalence, recognition of the disease is inadequate, underprioritized, and research is underfunded, contributing to diagnostic delays of 4 to 11 years. Therefore, the present study investigates the association between self-reported data and clinical presentation of endometriosis and aims to develop a phenotypic description of women with endometriosis. Using a big data approach, the data collected will be linked to existing registry-based information on endometriosis diagnosis and health care utilization. By unraveling the etiological aspects, we could identify patterns that may lead to categorizing novel clinical subgroups within the disease. This could enable earlier detection of endometriosis, thereby reducing current diagnostic delays. In addition, our study aims to identify different dietary components that may worsen the quality of life and pain in women with endometriosis, upon which we can make real-world data-driven nutritional recommendations. Ultimately, the findings from this multifaceted study have the potential to reduce diagnostic delays, improve patient care, and pave the way for more personalized and targeted approaches to managing endometriosis, marking a pivotal step toward enhancing the overall well-being of affected individuals.

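### The diet tests compare unadjusted score levels between self-selected diet-users and non-users, so they cannot show effects on change and can make a neutral or helpful diet look harmful

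*Protocol article*

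**What the plan says.** In the Protocol article, Statistical and machine learning analyses, two steps are named for diet. First, "independent samples t-tests will be conducted to see whether EQ-5D-5L, CSI-9 and EHP-5 scores were different between diet-users and non-diet users". Then "a one-way analysis of variance of no diet use and the various diets will be carried out for the EQ-5D-5L, CSI-9, and EHP-5 scores", with Tukey comparisons to locate differences. Cramér's V is added for associations among symptoms, severity, diet and lifestyle. None of these steps names a baseline score, a change score, a repeated-measures term or a covariate. The one method that explicitly uses the time series, the LSTM model, serves risk prediction in undiagnosed women.

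The aim is worded in two ways. The Introduction says "we aim to investigate the effects of dietary restriction of these components on changes in quality of life, pain, and central pain sensitization". The Secondary objectives say "To explore whether there is an association between removing or restricting dietary components and quality of life, pain, and central sensitization".

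Under Questionnaire, participants are asked to "complete a baseline questionnaire once and a longitudinal questionnaire monthly for one year". The topics include symptoms, medication, known conditions, socio-demographics and dietary habits.

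The intended use is directional. The Abstract says "we may identify dietary components that worsen the quality of life and pain in women with endometriosis", and the closing Conclusions plan to "identify different dietary components that may worsen the quality of life and pain in women with endometriosis". Both sections link this to nutritional recommendations.

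**The concern.** The study is non-interventional, so each woman decides whether to restrict food. A difference in score level between those who do and those who do not mixes any effect of diet with whatever led to the choice. Symptom severity is an obvious candidate. If it drives the choice, diet-users score worse before diet has done anything, and an unadjusted comparison cannot separate the two.

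The data to do better are largely planned: a baseline and a year of monthly questionnaires allow a woman to be compared with herself. The named tests do not use that. They answer whether diet-users score differently. The Introduction asks whether restriction changes scores, and the Conclusions ask which components make women worse. At stake is advice to patients that could point the wrong way, supported by a small P value from a large sample.

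Pain also belongs to the diet question in the Introduction and the Secondary objectives, but VAS appears in neither the diet t-tests nor the diet ANOVA. It is named only for the comparison of the endometriosis and reference groups.

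**Working it through.** The article gives no power, effect size or SD, so there is no figure of its own to reproduce.

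**Inputs from the article:** 5,000 women with endometriosis; significance at P < 0.05 (taken as two-sided).

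**Assumed, because the article does not give them:** the share of diet-users; the imbalance *b*, meaning the difference in mean score (in SD units) between diet-users and non-users that severity alone produces; the odds ratio for restricting per SD of severity; the within-woman correlation.

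**Step 1. False-positive probability when diet has no effect.** In SD units, SE = √(1/n_diet + 1/n_no diet), and P(significant) = Φ(b/SE − 1.96) + Φ(−b/SE − 1.96).

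For 30% diet-users: SE = √(1/1,500 + 1/3,500) = 0.0309. For b = 0.10: b/SE = 3.24, and Φ(3.24 − 1.96) = Φ(1.28) = 0.90; the second term is negligible. The difference detectable with 80% power is (1.96 + 0.84) × 0.0309 = 0.09 SD.

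| Diet-users | SE (SD) | Detectable at 80% power (SD) | b = 0.05 | b = 0.10 | b = 0.20 |
|---|---|---|---|---|---|
| 10% | 0.047 | 0.13 | 19% | 56% | 99% |
| 30% | 0.031 | 0.09 | 37% | 90% | 100% |
| 50% | 0.028 | 0.08 | 42% | 94% | 100% |

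**Step 2. Simulation of the planned comparison against a change analysis.** The setting is 5,000 women, 13 scores each (baseline plus 12), about 30% starting a diet after baseline, choice depending on stable severity, within-woman correlation 0.5 or 0.7, and 200 replicates per setting. Positive values mean that diet-users look worse. The unadjusted column covers the month-12 score and the follow-up mean. Change is the follow-up mean minus baseline. There is no true diet effect.

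| OR per SD of severity | Unadjusted difference (SD) | Unadjusted P < 0.05 | After adjusting for one baseline score (SD) | Change (SD) | Change P < 0.05 |
|---|---|---|---|---|---|
| 1.0 | 0.00 | 5–7% | 0.00 | 0.00 | 5–6% |
| 1.1 | 0.07–0.08 | 57–86.5% | 0.03 | 0.00 | 3–5% |
| 1.3 | 0.18–0.22 | 100% | 0.07–0.09 | 0.00 | 3.5–4% |
| 1.5 | 0.28–0.33 | 100% | 0.10–0.14 | 0.00 | 4.5–6.5% |

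**Step 3. Sign reversal.** With a true benefit of 0.10 SD, OR 1.3 and correlation 0.6, the unadjusted comparison shows diet-users about 0.10 SD worse, significant in 92% (month 12) to 98% (follow-up mean) of runs. The change analysis recovers the 0.10 SD benefit.

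Two readings follow. Adjusting for a single noisy baseline score removes only part of the bias. The change analysis is unbiased here because the simulated severity is stable and diet starts after baseline; neither is guaranteed in the real data.

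**The case against.** The strongest reply is that the formal secondary objective, like the Aims in the Abstract, speaks only of association. An unadjusted test can describe an association, and the study is exploratory and non-interventional. That stands for the objective as worded. It does not cover the Introduction, which asks about effects on changes, or the Conclusions, which look for components that worsen outcomes.

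Second, the article says that all its methods will also be run with diagnosed and undiagnosed women separated. A reader might infer that cases and controls are simply pooled and that diet use then stands in for diagnosis. The text does not support that without qualification, because the split is planned. However, it is one scenario among several, and it does nothing about severity differing among diagnosed women.

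Third, a fuller analysis plan may hold adjusted models. That is possible, but the article does more than leave the method open: it names the tests.

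Fourth, the proposed model does not remove reverse causation, because symptom flares can prompt restriction and also carry over to the next month. With zero diet effect, log-odds of restricting of 0.3 to 0.7 per SD of score and residual autocorrelation of 0.3 to 0.6 (all assumed), a lagged within-woman estimate still shows a spurious worsening of roughly 0.03 to 0.11 SD. This stands, and it limits what may be concluded even after the change.

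Other stronger readings also lack support. The article does not say that monthly records will be pooled as if independent, so no inflated error rate can be claimed on that ground. It does not tie the recommendations to these tests alone. The unadjusted comparison "The VAS scores of the endometriosis group and the reference group will be compared with independent sample t-tests" can stand as description; medication may follow from diagnosis, so adjusting for it could remove part of the difference being described.

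**Conclusion.** The point holds as a mismatch between a named method and the stated aim and use. Unadjusted between-women comparisons of score levels cannot show an effect of restriction on change and cannot support a statement that a component worsens outcomes.

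The bias is a possibility that depends on assumptions. A reader might infer that sicker women do restrict food and that a spurious diet effect will appear; nothing in the article shows either. What can be said is that the sample leaves little room for confounding. With 5,000 women and 10% to 50% diet-users, an imbalance of 0.1 SD gives a significant result in 56% to 94% of cases when diet does nothing. Under an odds ratio of 1.3 per SD, a real 0.10 SD benefit can appear as harm of about the same size. The objective is secondary, but advice to patients is meant to follow from this line of work.

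**What to change.** Among women with endometriosis, make the main diet analysis a linear mixed model of the repeated EQ-5D-5L, EHP-5, CSI-9 and VAS pain scores. Include a random woman effect and prior-month restriction split into within-woman and between-woman parts. Adjust for baseline score, age, medication and other confounders that the questionnaire records. Report the within-woman estimate with a 95% confidence interval. Keep the t-tests and ANOVA as descriptive, and analyse EQ-5D-5L and CSI-9 in controls separately. Word the conclusions as association, since the lagged estimate reduces reverse causation from flares but does not remove it.

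First confirm that the diet items and each scale are asked monthly; the questionnaires are in the Supplementary Data, and the article lists only topics.

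The cost is revised analysis wording and some extra analysis work. The confidence interval will be wider, because only women who change their diet during follow-up inform the within-woman estimate.
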